# I-KID study protocol: evaluation of efficacy, outcomes and safety of a new infant haemodialysis and ultrafiltration machine in clinical use: a randomised clinical investigation using a cluster stepped-wedge design

**DOI:** 10.1136/bmjpo-2021-001224

**Published:** 2021-10-18

**Keywords:** nephrology, neonatology, technology

## Abstract

**Introduction:**

The I-KID study aims to determine the clinical efficacy, outcomes and safety of a novel non-CE-marked infant haemodialysis machine, the Newcastle Infant Dialysis Ultrafiltration System (NIDUS), compared with currently available therapy in the UK. NIDUS is specifically designed for renal replacement therapy in small babies between 0.8 and 8 kg.

**Methods and analysis:**

The clinical investigation is taking place in six UK centres. This is a randomised clinical investigation using a cluster stepped-wedge design. The study aims to recruit 95 babies requiring renal replacement therapy in paediatric intensive care units over 20 months.

**Ethics and dissemination:**

The study has high parent and public involvement at all stages in its design and parents will be involved in dissemination of results to parents and professionals via publications, conference proceedings and newsletters. The study has has ethics permissions from Tyne and Wear South Research Ethics Committee.

**Trial registration numbers:**

IRAS ID number: 170 481

MHRA Reference: CI/2017/0066

ISRCT Number: 13 787 486

CPMS ID number: 36 558

NHS REC reference: 16/NE/0008

Eudamed number: CIV-GB-18-02-023105

Link to full protocol v6.0: https://fundingawards.nihr.ac.uk/award/14/23/26

What is already known on this topic??Babies in paediatric intensive care unit may develop acute renal failure and require therapeutic support.Renal replacement options for babies are limited because of their small size and limitations of technology.Current haemodialysis and filtration systems in use in UK are not recommended or licensed for children under 8 kg.

What this study hopes to add?Renal replacement methods for infants under 8 kg in paediatric intensive care unit will be compared.The efficacy, outcomes and safety of a new infant haemodialysis device will be assessed.Usability of the new device in normal clinical settings outside of the development centre will be examined.

## Introduction

Young babies requiring renal replacement therapy (RRT) present specific therapeutic challenges because of their small size and the current technology available. Publications indicate similar problems faced by clinicians worldwide who use adult devices because of lack of alternatives, and the need for solutions including improved device technology.^1 2^

This clinical investigation protocol is designed to determine the clinical efficacy, outcomes and safety of a novel non-CE-marked infant haemodialysis (HD) machine, the Newcastle Infant Dialysis Ultrafiltration System (NIDUS), compared with currently available RRT in the UK. NIDUS is designed for use in babies between 0.8 and 8 kg. There is evidence from a previous single-centre pilot study to anticipate NIDUS has the potential to contribute significant benefits to small babies needing RRT.^3^

The proposed clinical investigation is a result of a multicentre collaboration between clinicians, scientists, academics, with significant parent and public involvement, throughout its development; working with a manufacturing company, Allmed. The results will have potential to change clinical practice.

The NIDUS machine uses a smaller circuit volume than current devices. Pilot data from the development centre have suggested management of fluid overload and renal failure is possible for small infants, with the potential for reduced exposure to blood products, and more precise control of ultrafiltration (UF) and dialysis.^3^ Nurses have reported ease of use of the NIDUS within the design centre but this requires evaluation in standard clinical environments.

### Background

There are several populations of babies requiring RRT. Those included in this study are unwell infants in paediatric intensive care units (PICU), who mostly do not have intrinsic renal disease and therefore have good potential for renal recovery. Many are postoperative, especially postcardiac surgery, whose major problem is an acute kidney insult, fluid overload and poor urine output, and others who are septic or have renal failure as part of multiorgan failure. Although mortality and morbidity in PICU varies and is related to the underlying diagnosis, survival of babies in PICU is worse in those with fluid overload^4^ or needing RRT,^5^ of whom up to 20%–40% may die.^5–9^ RRT is supportive until kidney recovery and although most survivors are independent of RRT at discharge from PICU, data on chronic renal sequelae are lacking. Children requiring RRT in PICU have been reported to have longer length of stay and required more days of ventilator support.^8^ There are over 200 infants per year in the UK receiving treatment with continuous RRT (CRRT) in PICU.^10 11^

Some babies will be excluded—for example, those with an inborn error of metabolism such as urea cycle defects causing hyperammonaemia, as they require emergency, very rapid removal of toxic metabolites by higher than normal dialysis clearances,^12^ and babies with severe intrinsic renal disease, which is often congenital, who are usually treated with chronic peritoneal dialysis (PD) at home.

### Current RRT

PD is used frequently to support infants after open heart surgery.^5 13^ PD is technically simpler than HD; there is no lower size limit but complications are common in the smallest patients.^4^ UF is unpredictable, and chemical clearance less efficient, especially in unstable babies who develop splanchnic vasoconstriction and who also risk developing necrotising enterocolitis. This renders PD impossible, as does abdominal surgery and congenital abdominal wall defects. Larger critically ill infants with multiorgan failure are often treated with a variety of continuously delivered HD modalities (CRRT).^4 5 9^ Vascular access for HD modalities including continuous veno-venous haemofiltration (CVVH) is problematic as the size of central venous line required for adequate blood flow is disproportionately large for the size of the baby especially when a double lumen line is needed.

While there are no randomised controlled trials in infants, publications indicate recurring themes of difficulties with vascular access and blood flows, fluid balance, rapid clotting, loss of circuits and hypotensive episodes at initiation.^6–9^

Conventional HD and CRRT machines in the UK are used in PICU unlicensed as they are CE marked for use in adults and bigger children. Manufacturers quote fluid balance control as ±30 mL/hour,^14^ and they, therefore, are not licensed for babies weighing <8 kg (or approved for use in children of <20 kg in the USA). The recommended minimum 7-French, dual-lumen vascular access lines and continuous 40 mL/min blood flows are difficult to achieve in the smallest babies. Their relatively large circuit volume (50–70 mL) produces sudden dilution of blood on commencing treatment if crystalloid primed, and increases the risk of anaemia with circuit loss. Hypotension on connection is a reported problem.^6 15 16^ Blood priming risks exposing the baby abruptly to aberrant chemical and pH changes, which are reduced by predialysing the circuit.^17^ Exposure to blood transfusions increases the risk of developing tissue-type sensitisation which may be important if renal function does not recover and renal or other solid organ transplant is considered in the future.

There is one CE marked new device for smaller children, the CARPEDIEM, which is not yet available in the UK to enable comparisons,^18 19^ others, notably in USA, have adapted other adult devices like Aquadex.^9 20^

### NIDUS technology

In 1995, a group in Newcastle designed a novel HD circuit, which operated by different principles that is, by syringes, and uncoupled the baby’s blood flow capacity from the requirements of the dialysis filter.^21^ In 2005, they reported the results of automating this as a miniaturised machine (circuit volume less than 10 mL), with which four babies weighing under 4 kg were treated, using a single-lumen access line, and without the need for blood priming.^22^ This device was subsequently developed into NIDUS,^3^ which is used as the intervention device in the I-KID study. This clinical investigation will contribute to the current knowledge base and further understanding of the effects of RRT and address the need for improved technology to provide RRT effectively and safely for small babies.^1 23 24^

Safety monitoring is an important focus of this study. The NIDUS makes a downloadable constant recording of all activity data including volumes, flows, pressures, alarms and response to alarms so any alarm or event, however small, can be subsequently analysed. The NIDUS potentially provides a safer way of performing RRT on babies by using a novel circuit that allows precise ultrafiltrate control thus reducing the potential for errors in ultrafiltrate removal that would be trivial for larger children but are not for a baby. Its small circuit volume (<10 mL) potentially avoids the need for blood priming with stored blood which has associated immediate risks and long-term risks of developing sensitising antibodies.

## Methods and analysis

The study aims to evaluate the efficacy and precision of NIDUS in UF fluid removal and monitor adverse effects of RRT including use of blood product transfusion (table 1). It will also generate a safety profile in the application of NIDUS in the clinical environment.

**Table 1 T1:** I-KID study summary

Design	A multicentre, randomised clinical investigation using a cluster stepped-wedge design
Study interventions	Control: current renal replacement therapy (either peritoneal dialysis or continuous veno-venous haemofiltration)
	Experimental intervention: renal replacement therapy using the newcastle infant dialysis ultrafiltration system
Objectives	Primary: To compare the use of a novel haemodialysis device with conventional renal replacement therapy in babies under 8 kg treated in paediatric intensive care units
	Secondary objective: To compare the use of a novel haemodialysis device with conventional renal replacement therapy using the secondary outcome measures
Outcomes	Primary: Accuracy of fluid removal by technique and compared with prescription
	Secondary: Haemodynamic status Biochemical clearances No of ventilator free days Survival Completion of intended renal replacement therapy course Need for additional vascular or dialysis access Unplanned change in circuits Exposure to blood transfusion Bleeding events Anticoagulant use Parent/guardian experience Staff acceptability and usability of device
Study sites	Birmingham Childrens Hospital Bristol Childrens Hospital Evelina London Childrens Hospital Great Ormond Street Hospital Newcastle (Great North Children’s Hospital and Freeman) University Hospitals Southampton
Participants	Sample: Children 0.8–7.99 kg in PICU who require RRT for renal insufficiency or fluid overload
	Size: approx. 95
Study duration	Approx. 30 months (approx. 20 months recruitment)

PICU, paediatric intensive care unit; RRT, renal replacement therapy.

### Study design

The study uses a cluster randomised standard stepped-wedge (SW) design^25^ with four periods and three sequences (figure 1). The control periods use conventional therapy (PD or CVVH), with NIDUS used in intervention periods. Each site will be trained in setting up and using the NIDUS before switching to an intervention period. The design means that all participating centres will have the chance to use both treatments during the course of the study. PICU nurses will need to be competency assessed before each site can begin using the intervention; 24 hours on call nurse/clinician is provided from Newcastle for telephone support. Using an SW design permits the phased training on NIDUS and allows within-centre comparisons to contribute to the treatment estimate.

**Figure 1 F1:**
[figure not shown]
I-KID study design. NIDUS, Newcastle Infant Dialysis Ultrafiltration System; SW, stepped-wedge.

### Randomisation

Past records suggested that Great Ormond Street Hospital, Evelina and Southampton (the large centres) treat substantially more patients for RRT than Birmingham, Bristol and Newcastle (the small centres). To avoid large imbalances between the sequences, random permutation in R software was used to allocate one large and one small centre to each sequence. The statistician was blind to the identities of the centres during the allocation.

### Sample selection and outcomes

The study (summarised in table 1, box 1) will be conducted in six PICUs. Inclusion and exclusion criteria are shown in box 2. RRT use and events such as access line changes and blood transfusions will be recorded via the established daily PICANet enhanced renal audit reporting system.^11^ The weight of the dialysate bags will be measured pre and post dialysis to enable accuracy of fluid removal to be calculated and clearances calculated from measurement of blood and dialysate fluid urea, phosphate and enzymatic creatinine (figures 2 and 3). No additional samples will be taken from the patient for the purposes of this study—only results from routine tests and waste dialysate are needed.

Box 1I-KID study timeline1–3 months: site setup and study procedure training.4–24 months: case recruitment.Training for use of Newcastle Infant Dialysis Ultrafiltration System takes place in the weeks leading up to crossover from control to intervention by in-person sessions and ‘dummy’ set up and running of devices. Written instructions, pictorial users guides and short film clips were created and accessed by scannable QRS code to ensure up to date versions were used. In-person sessions were supplemented and replaced with videolink sessions to comply with COVID-19 pandemic-related restriction and refresher training offered as requested by sites and post COVID-19 pandemic shut down of all research activity March–November 2020.25–30 months: site close down visits, statistical analysis of data, writing reports and to begin dissemination of results to the scientific, medical and nursing community as well as to parent/public interest groups.1–30 months: management: monthly formal trial management group meetings (minuted) take place in person and by videolink.Site communication: monthly informal site discussions (documented summary) for principal investigators and site research and clinical teams to share experience and questions take place throughout via phone and videolink.

Box 2I-KID inclusion and exclusion criteriaInclusion criteriaPatients in paediatric intensive care unit (PICU) with a body weight of 0.8–7.99 kg kg (note: includes estimated body weight in emergency situation) who require continuous renal replacement therapy (RRT) for acute renal insufficiency or fluid overload as part of their standard clinical care.Person with legal parental responsibility for the patient provides written informed consent for the patient to take part in the study.**This may be after the patient has started dialysis in an emergency situation so as not to delay treatment.Exclusion criteriaPatient with known chronic renal failure already on established adequate RRT (this exclusion should not apply when chronic RRT has failed and patient requires acute RRT during the PICU admission).Patient already established on adequate RRT for whom entry into the study would require additional central venous access, if that access is not required in the view of the clinical team.Patient has an underlying (or clinically suspected) diagnosis of a metabolic disease, including hyper ammonaemia and no other indication for RRT.Clinician makes a clinical decision that the patient should not receive RRT using Newcastle Infant Dialysis Ultrafiltration System.

**Figure 2 F2:**
[figure not shown]
Patient data collection timeline: haemodialysis/filtration devices.

**Figure 3 F3:**
[figure not shown]
Patient data collection timeline: peritoneal dialysis. PD, peritoneal dialysis.

Using a study-specific questionnaire, parents/guardians will be asked about their experience and staff will be asked about acceptability and usability of the RRT device. Follow-up/outcome data will be sought from a routine clinic visit approximately 1 month after start of their RRT; this is to establish whether renal recovery took place: this will include clinical information obtained at discharge from PICU.

### Statistical considerations

#### Primary outcome

The primary aim is to compare the precision of the standard therapy and NIDUS to deliver the fluid removal rate prescribed by the treating physician. The primary outcome is based on the first available determination of fluid removal over a period exceeding 1 hour and within the first 48 hours of commencement of RRT: if the observed removal is *X* and the prescribed removal is *A*, the primary outcome is log|*X-A*|. The expected difference of this quantity between the treatment groups is the log of the ratio of the SDs of the determinations by the two methods. The method supposes that *X* follows a normal distribution with mean *A* and hence the variance of the outcome is 
$\pi^{2}/8$
.

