#### Sample size

Historical data suggested that annual recruitment to the large centres would be 14 patients, with 9 patients in each of Bristol and Birmingham and 3 in Newcastle. The sample size was determined to detect a ratio of the SDs under the standard therapy and NIDUS of three, with power at least 80% and two-sided type I error of 5%. A threefold improvement in the precision of fluid removal in this population would be sufficiently marked that it would be likely to change practice. The calculation used the methods in Matthews and Forbes,^26^ adapted to unequal cluster sizes, and found that four periods in the SW design, each of 4.5 months, gave a power of 80% with an assumed intraclass correlation coefficient (ICC) of 0.1% and 84% for an ICC of 0.05. It was believed that these represented conservative choices for the ICC.

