#### Secondary outcomes

Fluid removal data aggregated over the duration of RRT, or the first 48 hours if shorter, will be calculated. Biochemical clearances and ventilator-free days while on RRT will be collected. Binary outcomes are: survival (to 30 days and to discharge), haemodynamic status, whether RRT was completed as intended, need for additional vascular access and unplanned change in dialysis circuit, exposure to blood transfusion, bleeding from insertion line and anticoagulant use.

Responses to questionnaires (1) parent/guardian about their experience and (2) to staff regarding acceptability and usability.

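### The primary comparison uses only the first fluid-removal determination per baby; with the planned fixed-cluster model it has about 70–71% power, and a pre-specified supportive analysis of any repeat determinations could recover part of the loss

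*Protocol article*

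**What the plan says.** **Primary outcome** (Protocol article, Primary outcome): "The primary outcome is based on the first available determination of fluid removal over a period exceeding 1 hour", which must fall in the first 48 hours of treatment. With X the observed and A the prescribed removal, the endpoint is log|X−A|, and its expected difference between arms is the log of the ratio of the two SDs. On the distribution the section states: "The method supposes that *X* follows a normal distribution with mean *A* and hence the variance of the outcome is"; the value it gives is π²/8.

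**Further data.** Under Secondary outcomes: "Fluid removal data aggregated over the duration of RRT, or the first 48 hours if shorter, will be calculated". Under Sample selection and outcomes: "The weight of the dialysate bags will be measured pre and post dialysis". The article does not say how many qualifying determinations a baby will have. The two data-collection timelines are figures that are not reproduced in the text at hand.

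**Power** (Sample size): "The sample size was determined to detect a ratio of the SDs under the standard therapy and NIDUS of three". The target is 80% or more in a two-sided 5% test. Power is given as 80% and 84% at two values of the intraclass correlation (ICC).

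**Model** (Planned analysis): fixed effects for treatment, period and cluster. The fixed cluster effect was adopted because COVID-19 interrupted data collection. No power is given for this model.

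**The concern.** Under the article's own model, each baby contributes one draw with SD √(π²/8) = 1.11, while the effect sought is log 3 = 1.10. The noise in a single observation is as large as the effect. If all babies in an arm share one SD, that noise is purely measurement-to-measurement chance, which repetition reduces. Later determinations of the same baby would inform the same log SD ratio, yet the primary test does not use them.

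The secondary outcome does not fill the gap. If it is a total over the period, it gives one X−A per baby and so again one draw of log|X−A|. A mean of several log|X−A| values is a different and more precise summary.

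What is at stake is whether the trial can answer its main question. The Recruitment section reports 62 control babies and slower recruitment on NIDUS, so more information from the same babies may be the cheapest gain still open.

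**Working it through.** **Inputs**

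- Effect: log 3 = 1.0986. Variance of one determination: π²/8 = 1.2337. Two-sided 5% test (Primary outcome; Sample size).
- Accrual: "annual recruitment to the large centres would be 14 patients, with 9 patients in each of Bristol and Birmingham and 3 in Newcastle". The 14 is read as per large centre: 3×14 + 9 + 9 + 3 = 63 a year, and 63 × 1.5 = 94.5 over 18 months, which matches the planned 95.
- Four periods of 4.5 months and three sequences, with one large and one small centre in each. Babies per centre-period: 14 × 4.5/12 = 5.25 (large), 3.375 (Bristol, Birmingham), 1.125 (Newcastle).
- Which small centre is in which sequence is not stated, so all allocations were tried.

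**Step 1: the stated power, one determination per baby.** This uses generalised least squares on the 6 × 4 centre-period means, with period effects and a random centre effect. The residual variance is π²/8 and the centre variance is (π²/8)·ICC/(1−ICC). Power = Φ(1.0986/SE − 1.96).

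| ICC | Newcastle in middle sequence | Other allocations |
|---|---|---|
| 0.05 | 83.8% | 81.7% |
| 0.1 | 80.4% | 78.6% |
| 0.001 (as printed, 0.1%) | 90% | 88% |

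The stated 84% and 80% are reproduced at ICCs of 0.05 and 0.1, so the printed 0.1% looks like a misprint for 0.1. One determination per baby therefore does meet the target under the model used for sizing.

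**Step 2: the planned model, one determination per baby.** The cells and variance are the same, but the centre effects are fixed.

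- Newcastle in an outer sequence: variance of the treatment effect = 0.1554 × 1.2337 = 0.1917, SE = 0.438. Then 1.0986/0.438 − 1.96 = 0.55, which gives 71%.
- Newcastle in the middle sequence: 0.1506 × 1.2337 = 0.1858, SE = 0.431, which gives 72%.
- With a t reference on 95 − (1 + 4 + 5) = 85 df: 70% and 71%.

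Only the treatment of the centre effect changed between the two steps, so it accounts for the fall.

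**Step 3: two determinations in every baby (assumption).** With r the within-baby correlation of log|X−A|, the variance of a baby's mean is (π²/8)(1 + r)/2. For example, at r = 0.5, SE = 0.438 × √0.75 = 0.379, and 1.0986/0.379 − 1.96 = 0.94, which gives 83%. Results with Newcastle in an outer sequence (the middle sequence adds up to about 1.3 points):

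| r | Power, normal | Power, t with 85 df |
|---|---|---|
| 0 | 94.4% | 93.9% |
| 0.1 | 92.3% | 91.7% |
| 0.3 | 87.5% | 86.8% |
| 0.5 | 82.6% | 81.7% |
| 0.7 | 77.7% | 76.7% |
| 1 | 70.9% | 69.9% |

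**Step 4: plausible values of r.** In simulation under the article's normal model, correlations of 0.5, 0.7 and 0.9 between a baby's raw errors X−A give r of about 0.11, 0.24 and 0.51. Taking log|·| weakens correlation considerably. The corresponding powers are about 92%, 89% and 82%.

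**Step 5: less favourable conditions.**

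- If only half the babies have a second determination, power is about 83%, 79% and 77% at r = 0, 0.3 and 0.5.
- If the 95 split as 62 control and an assumed 33 NIDUS, one determination gives 68–69%. Two give about 94% at r = 0.
- If, with that split, babies also differ in their own SD (variance of log SD 0.4), power rises only from 57% to 77%.

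**The case against.** **The single determination is not the cause of the shortfall.** A reader might infer that keeping one determination is why power is about 70%. Step 1 shows otherwise, since the same endpoint gives 80–84% with a random cluster effect. This objection stands in full.

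**94% is a ceiling.** It needs a second usable determination in every baby, one SD shared by all babies in an arm, and no within-baby correlation. None of these is in the document. This also stands, so the gain must be given as a range that includes no gain.

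**Separate repeat determinations may not exist.** The aggregated outcome could be one total, and the bag weighing is described only as before and after dialysis. This stands in part. An outcome defined as the earliest available measurement, with a secondary outcome over up to 48 hours, makes later data likely but does not prove that they are recorded separately.

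**Using the first determination is defensible.** It avoids informative numbers of repeats (through RRT duration, circuit loss or death) and measurements taken after a change of method. A 48-hour mean has the same target only if each arm's SD is stable over that time and across determinations of different length. Redefining the primary outcome of an open-label trial after 62 controls also costs credibility. This stands against replacing the primary outcome. It does not stand against a pre-specified supportive analysis.

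**The secondary outcome already covers it.** This holds only partly, because an aggregate is not a mean of log|X−A|.

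**Conclusion.** The point holds in limited form. Under the planned fixed-cluster model, one determination per baby gives about 70–71% power at planned sizes for an SD ratio of 3 (up to 72% with a normal reference and the better allocation), against a target of at least 80%. The change to fixed cluster effects produces the loss. Repeat determinations are a way to recover some of it. With two per baby, power would lie between no gain (r = 1) and about 94% (r = 0), with 82–83% at r = 0.5 and 77–78% at r = 0.7.

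These figures rest on the article's normal model with mean A, planned accrual, and an assumed second determination in every baby. The documents do not support reading the outcome definition as an error, 94% as the expected power, or the primary outcome as in need of replacement.

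**What to change.** Keep the primary outcome on the first qualifying determination. Before any comparison by arm, add in a dated amendment or in the analysis plan:

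- a lead supportive analysis of the same log SD ratio, using each baby's mean of log|X−A| over all determinations exceeding 1 hour in the first 48 hours;
- the same linear model, with fixed effects for treatment, period and cluster;
- an allowance for unequal numbers per baby, either by weights or by a within-baby term on the individual determinations;
- reporting beside the primary result, with the number of determinations per baby by arm.

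**Cost.** Some wording, and no new measurements provided that later determinations are recorded separately; the sponsor should confirm this first.

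**Downsides to state.** The mean equals the primary estimand only if each arm's SD is stable over 48 hours. The number of determinations may differ by arm. Later ones may follow a change of method. The supportive analysis also leaves the power of the primary test itself at about 70–71%, and the plan should say so.

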### Planned analysis

Analysis of all available data will be on the basis of intention-to-treat. A subgroup analysis will compare NIDUS with conventional CVVH that is, excluding PD. For the latter group the amount of fluid removed (*X*) will be compared with the amount the machine reports to have been removed (*A*).

The primary outcome will be analysed using a linear model with fixed effects for treatment, period and cluster. The use of a fixed rather than random effect for cluster is a response to the interruptions to data collection due to the effect of COVID-19 on PICUs and the subsequent difficulty in defining a suitable dispersion structure. Sensitivity analyses will use a generalised estimating equation and will assess the assumptions about *X*. If these are untenable then *X-A* will be modelled directly, with treatment dependent variances for the error terms. The above linear model will be applied to the non-binary secondary outcomes. Binary outcomes will be analysed using generalised mixed models if possible but using simple tabulations if more sophisticated analyse are infeasible. Questionnaire data will be tabulated by treatment.

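### The primary outcome does not say whether fluid removal is a rate or a volume over an unfixed window, and takes no account of body weight, so the contrast need not be the log SD ratio and π²/8 is a minimum variance

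*Protocol article*

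**What the plan says.** All references are to the protocol article.

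- **Primary outcome**, aim: to compare how precisely the two therapies manage "to deliver the fluid removal rate prescribed by the treating physician".
- **Primary outcome**, definition: X is the observed and A the prescribed removal, and the outcome is log|X−A|. It comes from the "first available determination of fluid removal over a period exceeding 1 hour and within the first 48 hours of commencement of RRT". No units are given, and nothing is divided by hours or kilograms.
- **Primary outcome**, interpretation: X is taken as normal with mean A. The expected difference between groups is equated with the log of the ratio of the two SDs, and the variance is set at π²/8.
- **Planned analysis**, subgroup without PD: "the amount of fluid removed (*X*) will be compared with the amount the machine reports". Here X is an amount.
- **Planned analysis**, model: "The primary outcome will be analysed using a linear model with fixed effects for treatment, period and cluster". If the assumptions about X fail, X−A is modelled directly with error variances that depend on treatment.
- **Box 2**: eligible babies have a "body weight of 0.8–7.99 kg".
- **Current RRT**: the only device error quoted is ±30 mL/hour.

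**The concern.** The aim, the outcome and the stated variance do not fit together. On the log scale, anything that multiplies the error becomes an additive term in the outcome. A baby measured over a longer window, or a larger baby with proportionately larger errors, has a higher expected log|X−A| whatever the device.

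Two consequences follow.

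- **Contrast.** If X and A are volumes and windows differ in length between arms, that difference is added to the treatment effect. Window length arises after allocation and could follow modality: the captions of figures 2 and 3 give PD its own data collection timeline, and PD occurs only under control. Weight is a baseline variable, so it moves the contrast only through chance or selection. Otherwise it adds noise.
- **Variance and power.** π²/8 is the variance of log|X−A| only when one SD applies to every baby in an arm. Variation in that SD between babies adds to it.

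The planned fallback does not cover this, because it lets the error variance depend on treatment but not on window or weight.

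**Working it through.** **Inputs from the article.** Annual recruitment is 14 in each of three large centres, then 9, 9 and 3. There are four periods of 4.5 months and three sequences, each with one large and one small centre. The target SD ratio is 3 (log 3 = 1.0986), two-sided α is 0.05, and the outcome variance is π²/8 = 1.2337.

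**Reproducing the plan's figures.**
- N = (3×14 + 9 + 9 + 3) × 1.5 years = 63 × 1.5 = 94.5, which agrees with 95.
- Power = Φ(log 3/SE − 1.96), with SE from generalised least squares on the stepped-wedge model with a random cluster effect. At ICC 0.05 this gives 83.6–85.6% with π²/8 as the total variance and 81.7–83.8% with it as the within-cluster variance. The stated 84% is reproduced. The ranges reflect which sequence holds the smallest centre.
- With the fixed cluster effects now planned, SE is 0.431–0.438, so log 3/SE = 2.51–2.55 and power is 71–72%. That drop is a separate matter. It is the baseline here because it is the planned model.

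**Model for the point.** Let T be window length and W weight. Then

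log|X−A| = log(SD of the arm) + k·log T + m·log W + log|Z|, with Z standard normal.

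For volumes, k = 0.5 if hourly errors are independent and k = 1 if an error in rate persists through the window. The treatment contrast equals

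log(SD ratio) + k × (difference in mean log T) + m × (difference in mean log W),

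and, with T and W varying independently, the variance is π²/8 + k²·Var(log T) + m²·Var(log W).

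**Window difference (assumed; the article gives no window lengths).** Take equal hourly precision in both arms and geometric-mean windows twice as long under control.
- k = 0.5: apparent SD ratio √2 = 1.41.
- k = 1: apparent SD ratio 2.0.
- The chance of a significant result with no true difference, under the fixed-effects model, is about 12–13% for k = 0.5 and 35–36% for k = 1.
- If NIDUS windows are twice as long instead, a true ratio of 3 appears as 3/1.41 = 2.12 or 3/2 = 1.5.

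**If X and A are rates.** Dividing by T replaces k by k − 1. A persistent rate error (k = 1) then cancels exactly. With independent hourly errors (k = 0.5) the exponent becomes −0.5, so control windows twice as long give an apparent ratio of 1/1.41 = 0.71. Using rates removes the proportional part but not all dependence on the window.

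**Weight spread (assumed: error proportional to weight, m = 1, weights log-uniform over 0.8–8 kg, no arm difference).**
- Var(log W) = (ln 10)²/12 = 0.442.
- Outcome variance = 1.234 + 0.442 = 1.676, which is 1.36 × π²/8.
- log 3/SE is multiplied by √(1.234/1.676) = 0.858, giving 2.15–2.19 and power of 58–59%, against 71–72% without the spread.

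**Window spread (assumed, no arm difference).** Windows log-uniform over 1–4 h have Var(log T) = (ln 4)²/12 = 0.160. This adds 0.04 (k = 0.5) or 0.16 (k = 1), and fixed-effects power becomes about 70% or 66%. Short, similar windows therefore cost little.

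**The case against.** The strongest reply is that the article never says X and A are volumes. The aim speaks of a rate, and the word amount appears only for the subgroup comparison, where A is redefined as the machine's own report. The full protocol or the SAP may give units and the measurement schedule. This stands as far as it goes: the volume reading is conditional. The ambiguity nevertheless lies in the article's own definition of its primary outcome, and a rate still leaves weight unscaled and its SD dependent on the window.

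A reader might infer that the outcome favours NIDUS, for example by supposing control windows three times as long, which under proportional growth would yield the whole target ratio of 3. The article does not support that. It gives no window lengths, and NIDUS windows could be the longer ones. The caption of figure 2 suggests that NIDUS and CVVH share a timeline, with only PD separate, and the subgroup analysis excludes PD. A reader might also take 48 hours as a typical window. It bounds when the determination falls, and a first available determination may be much shorter.

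The weight figure is likewise an assumption. The one device error quoted is a flat hourly figure, not per kilogram, and enrolled weights need not fill the eligible range.

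Finally, the linear model estimates its own residual variance, so an understated π²/8 does not invalidate the test. That is right: the understatement costs power, and only an arm difference in window or weight causes bias.

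**Conclusion.** The point holds as a defect of definition with a conditional consequence. The aim is a rate, the outcome is removal over an unfixed window, and the model has no term for window or weight. The contrast equals the log SD ratio only if mean log window and mean log weight match between arms, or do not scale the error. With X normal about A, π²/8 is the smallest value the outcome variance can take, reached only if one SD applies to every baby in an arm.

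No bias is demonstrated, and its direction is unknown. On the assumed twofold window difference the apparent ratio is 1.4 to 2.0 with no true difference in hourly precision. On the assumed weight spread, fixed-effects power falls from about 72% to about 59%. With error that depends little on weight and short, similar windows, both effects are small.

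**What to change.** 1. Define X and A as rates in mL/h over the same window, in the primary outcome and in the secondary outcome aggregated over up to 48 hours. This is a wording change. Window times are needed anyway to compare a measured volume with a prescribed rate.
2. Add log(body weight) to the primary linear model. Weight is an entry criterion and already collected. The cost is one degree of freedom.
3. Report window length by arm and by modality (PD, CVVH, NIDUS), so that readers can judge whether the windows are comparable.
4. Use log(window length) as a covariate in a sensitivity analysis only. It is set after allocation and may be nearly collinear with treatment. If windows differed threefold between arms, with an assumed within-arm log-window variance of 0.2, the treatment variance would rise by a factor of about 1.4 and fixed-effects power at residual variance π²/8 would fall from about 72% to about 57%.
5. Describe π²/8 as a lower bound that is attained only if one SD applies to all babies in an arm, and the stated power as the value at that bound.
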